### Statistical power analysis

Minimum detectable effect sizes were estimated using NCSS PASS [80] for the primary analyses proposed to fulfill primary specific aims 1 and 2. Assuming a 20% attrition rate between the end of the *Original Bridges study* (July 2017; N = 1249) and the *Bridges-R2* study (July 2022), our starting N for *Bridges-R2* will be 999 participants. Following a maximum attrition rate of 20%, we anticipate a minimum of 799 participants available at the final measurement wave. We further assume alpha = .017 and power = .80. For specific aim 1, we assumed a control group HIV prevalence of 19.7% based on published data for 15–24-year-old youth from the same geographic region [81] and an intraclass correlation (ICC) of .12 based on our current *Bridges* study data. Assuming these inputs, a two-level multilevel model would be able to detect a raw proportion difference of 15.3%, which corresponds to a standardized difference *h* = .499, which is a medium minimum detectable effect size [82]. For specific aim 2, we computed the minimum standardized mean difference *d* for a continuous mechanism of change outcome in a three-level multilevel model assuming the same inputs as above and a maximum within-participant ICC of .70 for the continuous change mechanisms in the *Bridges* study. Under these conditions, *d* = .462, which is a medium minimum detectable standardized mean difference [82].

### Ethics and consent

All study procedures were approved by the Washington University in St. Louis Review Board (IRB # 201703104) and by in-country local IRBs in Uganda: Uganda Virus Research Institute- UVRI (GC/127/900), and Uganda National Council of Science and Technology -UNCST (SS2586). Amendments to the study protocol will be submitted for approval to the above-mentioned IRBs. Participation in the *Bridges-R2 study* will be voluntary. Written informed consent will be obtained from all participants. This will be done prior to assessment. In the consent form, it will clearly be stated that the participant can: withdraw from the study at any time, for any reason, with no explanation, and would not be penalized in any way; refuse to answer any questions at any time; review any materials and request that we erase any of their responses; make inquiries and address complaints to Secretary of the Ethics Committee at UVRI, UNCST, and Washington University in St. Louis. Participants will also be told of the potential risks and benefits of participating in the study. Each participant will receive a copy of the signed consent form.

### Data collection

#### Quantitative assessments

Assessments will occur at baseline following reconsenting, 12, and 24-months and will take place at the ICHAD’s field offices in Masaka or satellite sites (including health clinics) for study collaborators: Mildmay or Reach the Youth (RTY) Uganda, with each lasting about 60–90 minutes. Interviews will be conducted by interviewers fluent in Luganda and English depending on participant’s English proficiency. A list of standardized instruments that will be included in the main statistical analyses are outlined in Table 2. All measures used have been pre-tested and made culturally appropriate to the Ugandan context in our ongoing Suubi+Adherence-R2 study [79]. Assessments capturing non-sensitive information, for example, sociodemographic information, mental health functioning, psychosocial well-being and social support are administered orally but recorded using Qualtrics–a computer assisted survey implementation program.

**Table 2 pone.0284572.t002:** *Bridges-R2* study measures.

Variable	Measurement	Timepoint
**Demographics**		
Socio-demographics: Age; sex (assigned at birth), orphanhood status; socioeconomic status; family composition		**T1-RC, 12, 24
**Moderators**		
Rural/semi-urban; exposure to outside HIV-related programs; household income; asset accumulation		**T1-RC, 12, 24
**Potential Mechanisms of Change**		
Self-efficacy	Adapted Tennessee Self-Concept Scale (TSC-2) [83]	**T1-RC, 12, 24
Social Support	Social Support Behaviors Scale (SS-B) [84] Family Cohesion Scale [85]	**T1-RC, 12, 24
Hopelessness	Beck Hopelessness Scale [86]	**T1-RC, 12, 24
Stigma and Isolation	Adapted Social Impact Scale [87]	**T1-RC, 12, 24
Self-esteem	Rosenberg Self-Esteem Scale [88]	**T1-RC, 12, 24
Transition milestones (residential independence, education, employment, parenthood, prosocial transition, relationship/marital status)	Relationship assessment scale [89,90] Additional prosocial activities, Demographics, Work history interview	**T1-RC, 12, 24
Access to services	Treatment Services Review (TSR) adult versions [91,92]	**T1-RC, 12, 24
Substance misuse	Alcohol, Smoking, Substance Involvement Screening Test [93]	**T1-RC, 12, 24
**Primary Outcome**		
HIV prevalence	Biological assay	**T1-RC, 12, 24
**Secondary Outcomes**		
Sexual risks	Timeline Follow Back (TFLB) [94,95], Adapted Youth Aids Prevention Project (used in Suubi & CHAMP) [96]	**T1-RC, 12, 24
Mental Health Functioning	Center for Epidemiological Studies-Depression Scale (CES- D) [97], PTSD Checklist [98], Brief symptom inventory [99]	**T1-RC, 12, 24
Financial/economic stability (Savings and asset)	Verifiable Bank statements, MIS IDA [100,101]; Self-Reports	**T1-RC, 12, 24
Adherence (for YLHIV)	Wilson self-report Questionnaire [102], viral load	**T1-RC, 12, 24
HIV testing	Self-report, verified by clinic records	**T1-RC, 12, 24
PrEP use (for HIV negative participants)	Self-report, verified by clinic records	**T1-RC, 12, 24
Medical Male Circumcision (for boys)	Self-report, verified by clinic records	**T1-RC, 12, 24

** T1-RC–Time 1 immediately following re-consenting.

#### Biological assay

Mildmay, with internationally accredited laboratories by SANAS (https://www.sanas.co.za) will be responsible for collection of all biomarkers, participants’ counseling, notification, referral for treatment, follow-up and monitoring procedures for biological testing for HIV and viral load. Biological assay will be collected at T1 following reconsenting (T1-RC), and at 12 and 24-month post-reconsenting by Mildmay Medical Staff. HIV test results will be communicated to the participants by Mildmay.

#### Qualitative data collection

Semi-structured qualitative interviews will be conducted at one time point (T1) immediately following the completion of quantitative assessments at T1-RC. The interviews will focus on participants’ experiences with the *Original Bridges* study, plus an exploration of: 1) key multi-level factors that may have affected participants’ decision-making and behaviors around savings and sexual risk taking; 2) social transitions and their impact on sexual risk taking, saving, and mental health; and 3) perceptions of costs and rewards of saving and safe sexual behaviors. We will explore whether these experiences and perceptions differ between participants in the control and intervention arms. For participants in the two treatment arms only, we will address their experiences with the intervention and its specific components; and key multi-level factors (individual, family, and programmatic) that may have impacted their participation in the intervention. Using quantitative data obtained at T1-RC, a stratified purposeful sampling strategy [103] will be used to select a total of 60 participants (n = 20 per study arm) from the highest and lowest quartiles on two key outcomes (sexual risk-taking and mental health). The selected 60 participants will be invited to participate in the semi-structured interviews. These numbers will be sufficient to achieve theoretical saturation [103–105]. Moreover, the sampling strategy will ensure that participants with varying experiences within the same study arm are represented; and allow for identification of common patterns and variations in participants’ experiences (e.g., unique vulnerabilities and protective factors). The semi-structured qualitative interviews will be conducted in English or Luganda based on participants’ preference. Questions will be translated (English to Luganda) and back-translated by two proficient team members. Questions will be reviewed by two native speakers to make sure that they sound natural and conversational, and revised accordingly. Each interview will last about 60 minutes and will be audio-taped.

### Data analysis plan

#### Data quality assurance, initial analyses, and missing data

We will use MIS IDA Q [101] to check for data-entry errors, missing values, and accounting inconsistencies. Frequency tables for all variables and measures of central tendency and variability for continuous variables will characterize the sample overall and by randomization group. We will address incomplete data with direct maximum likelihood (ML) and multiple imputation (MI) [106] because they make the relatively mild assumption that incomplete data arise from a conditionally missing-at-random (MAR) mechanism [107]. Auxiliary variables will be included to help meet the MAR assumption [108,109] and sensitivity analyses will be conducted with pattern-based MI [110,111] to assess the robustness of the MAR assumption. [112]. SAS [113] and Mplus [114] will be used to perform the proposed analyses.

#### Time points used in proposed inferential analyses

To maximize the rigor of the analyses; to assure alignment of biomarker data (only measured in the *Bridges-R2*) and our remaining outcomes; and to avoid reuse of *Original Bridges* study outcomes (already examined for shorter-term intervention efficacy) and biased examination of longer-term intervention efficacy, all proposed primary inferential analyses and most of the proposed secondary inferential analyses listed will use only *Bridges-R2* data. The exception is longitudinal developmental trajectory analyses proposed to explore associations between changes in time-varying covariates and mechanisms of change with outcomes measured across both studies.

#### Primary analyses for Aim 1

We hypothesize that: H1a. Relative to the control group, participants in the *Bridges* intervention group (1:1 savings incentive match rate) will have a lower odds of HIV infection at the final measurement point; H1b. Relative to the control group, participants in the *Bridges PLUS* intervention group (1:2 savings incentive match rate) will have a lower odds of HIV infection at the final measurement point; and H1c. Relative to the *Bridges* intervention group, participants in the *Bridges* PLUS intervention group will have a lower odds of HIV infection at the final measurement point. To test H1a-H1c, we will fit a two-level generalized linear mixed model (GLMM) with fixed effects for study arm, time, and their interaction. We will use random intercepts for school ID to account for clustering of persons within schools. Reflecting the binary HIV status outcome, a binomial distribution and logit link will be used. To test H1a-H1c we will perform three pairwise planned comparisons. Alpha (α) will be set at .05/3 = .017 for these three comparisons to maintain a nominal α = .05. We will adjust for orphanhood status, the only covariate where imbalance was detected in our *Original Bridges* data. It is important to note that previously, deaths have been very few; however, if numbers of deaths become non- trivial, we will extend our proposed GLMMs to jointly model survival and the odds of HIV infection simultaneously [115].

#### Secondary exploratory analyses for Aim 1

Exploratory analyses will explore for all participants the superiority of a) *Bridges* to control, b) *Bridges PLUS* to control, and c) *Bridges PLUS* to *Bridges* in lowering the odds of engaging in sexual risk taking, the odds of problem alcohol and substance use behaviors, and increasing mean levels of mental health functioning among study participants. Subgroup analyses will perform the same comparisons for HIV testing and PrEP use for the subset of participants not living with HIV; a parallel set of analyses will perform the same comparisons for ART adherence and HIV care engagement for youth living with HIV. The same GLMM approach described above will be extended to three levels to model the odds of binary outcomes across time using the same fixed effects (study arm, time, and study arm-by-time), a random effect for the school level (random intercepts), and adding random effects for the person level (random intercepts, random slopes, and their covariance). For the continuous mental health exploratory outcomes, we will fit linear mixed models (LMMs).

To maximize rigor, the assumptions of normality and constant variance of residuals in LMMs will be evaluated by examining histograms of the residuals and scatter plots of predicted values-by-Cholesky-scaled residuals, respectively. Transformations of outcomes will be utilized as needed to improve data conformance with model assumptions. Inferences for models whose residual statistics still do not fully meet assumptions following transformations will be generated via robust heteroskedastic-consistent estimators [116]. Group comparisons will be performed via three pairwise time-averaged comparisons across repeated measurements. Alpha (α) will be set at .05/3 = .017 to maintain a nominal α = .05 per outcome. Any additional post-hoc comparisons (e.g., paired comparisons of groups at each time point) will maintain nominal α = .05 through the use of simulation-based stepdown multiple comparison methods [117]. All analyses will include outlier and influential case screening via computation of Cook’s D, DFBetas, and likelihood displacement statistics. If outliers are found, results will be reported with and without outliers included [118,119].

#### Primary analyses for Aim 2

We hypothesize that: H2a. Relative to the control group, participants in the *Bridges* intervention group (1:1 savings incentive match rate) will have higher mean levels of economic stability, positive youth transitions, and social support during the *Bridges-R2* study; H2b. Relative to the control group, participants in the *Bridges PLUS* intervention group (1:2 savings incentive match rate) will have higher mean levels of economic stability, positive youth transitions and social support in the Bridges-R2 study, and; H2c. Relative to the *Bridges* intervention group, participants during the *Bridges PLUS* intervention group will have higher mean levels of economic stability, positive youth transitions and social support. The same three-level linear mixed model (LMM) approach as described in the previous paragraph will be used to test these hypotheses. Group comparisons will be performed via three pairwise time-averaged comparisons across repeated measurements. α will be set at .05/3 = .017 to maintain nominal α = .05 per outcome.

### Secondary exploratory analyses for Aim 2

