#### Progress of the *Original Bridges* study

*Economic stability*. The study filled important knowledge gaps on the effect of savings- led EEI on short-term economic stability. We found that several measures of material well‐being improved among participants in the treatment condition [74]. Specifically, *Bridges PLUS* arm participants had significantly lower odds of having only a few sets of clothes at both the 12‐month (OR = 0.49, 95% CI = 0.24, 0.97) and 24‐month follow‐ ups (OR = 0.36; 95% CI = 0.15, 0.85) compared to participants in the control group. In addition, *Bridges* arm participants had significantly lower odds of having no blanket at both the 12‐month (OR = 0.33; 95% CI = 0.12, 0.89) and 24‐ month follow‐ups (OR = 0.19; 95% CI = 0.06, 0.64) compared to participants in the control group [71]. In addition, the intervention increased the odds of owning a family business and the levels of asset holding. Families in both *Bridges* and *Bridges PLUS* arms had significantly higher odds of owning a small business at the 24‐month follow‐up (for *Bridges*: OR = 2.28; 95% CI = 1.05, 4.95; for *Bridges PLUS*: OR = 2.95; 95% CI = 1.38, 6.29) than families in the control arm. Both treatment arms reported a higher increase in their levels of asset possession from baseline to 12 months than the average increase in the control arm [10,74].

*Mental health functioning*. At 24-months post intervention initiation we found a significant unmediated effect of the intervention on children’s mental health (B = −0.59; 95% CI = 0.93, −0.25; p < 0.001; β = −0.33). Moreover, the results suggest that participation in the intervention reduced child poverty at the 12-month follow-up, which in turn improved latent mental health outcome at 24 months (B = −0.14; 95% CI: −0.29, −0.01; p < 0.06; β = −0.08). In addition, at 36 and 48-months, mental health of children in the treatment arms improved by 0.13 and 0.16 standard deviation points correspondingly with no evidence of mediation [75].

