## Methods

### The current study

The *Bridges-R2* study will examine the longitudinal developmental and health outcomes [(e.g., sexual risk-taking behaviors, HIV antiretroviral therapy adherence, PrEP use (for those who are HIV negative)], optimizing health outcomes along the HIV care continuum, and potential mechanisms of the effect of protective health behaviors) of the *Bridges* cohort. Specifically, based on emerging adulthood [13,14] and asset theory [59,60], we expect that the Bridges program would impact youth developmental and health outcomes by reducing the vulnerabilities associated with orphanhood which interfere with the normal development, including reducing stigma and discrimination, improving family support, social support, hopefulness, general self-efficacy, and improve sexual communication skills, and overall facilitate healthier transitions into adulthood (see Fig 2A and 2B). The data will be collected at baseline following reconsenting, 12, and 24-months.

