#### Exploring trajectories of change over the full developmental period captured by the *Bridges* project

Moderator, mediator, and sexual behavior and mental health outcome data will be available at 8 time points from the start of *Original Bridges* through the end of *Bridges-R2*. We will initially explore trajectories of these variables by generating spaghetti plots of participants’ individual trajectories with intervention group averages overlaid to visualize group average (i.e., mean) levels of change and inter-participant variability. Next, we will fit mixed effects growth models to investigate whether change over time can be quantified using low-dimensional parametric functions (e.g., linear, quadratic) of explanatory variables. Finally, we will employ the highly flexible time-varying effect modeling (TVEM) to go beyond simple parametric functions to describe the form of changes in variables over time. TVEM allows the effects of covariates on outcome trends to vary over time non-parametrically [122,123]. TVEMs will be fitted using the % weighted TVEM SAS macro produced by the Penn State Methodology Center, a leader in developing longitudinal analysis methods and software.

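### The Bridges-R2-only rule bars adjustment for the original baseline value of the outcome in the Aim 2 and mental-health models, for a reason that fits only the later original waves

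*Protocol article*

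**What the plan says.** The section on time points used in the inferential analyses sets a rule: "all proposed primary inferential analyses and most of the proposed secondary inferential analyses listed will use only *Bridges-R2* data". It gives as reasons rigour, alignment with biomarkers measured only in R2, and not reusing original outcomes already examined for shorter-term efficacy. It allows one departure, for work that spans the two studies: "The exception is longitudinal developmental trajectory analyses proposed to explore associations between changes in time-varying covariates and mechanisms of change with outcomes".

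Under the secondary exploratory analyses for Aim 1, the three-level models are built "using the same fixed effects (study arm, time, and study arm-by-time"), with random effects for school and person. The primary Aim 2 analyses (H2a-H2c: economic stability, positive youth transitions, social support) take over the same approach and compare arms by time-averaged contrasts at alpha .017. The one covariate named anywhere appears under the primary Aim 1 analysis, on the strength of a balance check in the earlier study: "We will adjust for orphanhood status, the only covariate where imbalance was detected in our".

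On visits, the article says: "The data will be collected at baseline following reconsenting, 12, and 24-months". On timing and numbers, the power section gives "July 2017; N = 1249) and the *Bridges-R2* study (July 2022), our starting N for *Bridges-R2* will be 999 participants". On what is already held, the trajectory section, which runs to the last R2 visit, says: "Moderator, mediator, and sexual behavior and mental health outcome data will be available at 8 time points from the start of *Original Bridges".

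**The concern.** The rule is wider than its reason. Waves 2 to 5 were measured after the arms had diverged, and their outcomes have been analysed for efficacy, so keeping them out of the long-term tests is defensible. The original baseline is different. It precedes the intervention, carries no treatment effect, and would be used as a covariate and not as an outcome. Alignment with biomarkers concerns when outcomes are measured and says nothing against a pre-intervention covariate either.

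This is a stated rule and not a detail left open, so an analysis plan that follows it could not put the Wave 1 value of the outcome into the H2 or mental-health models. At stake are precision on H2a-H2c, which the protocol labels primary, and some protection against imbalance between arms. Such imbalance can arise by chance with 16 schools per arm, or through who re-consents.

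**Working it through.** **Are Wave 1 values held?** Table 1 lists five original waves (baseline with N = 1383, then Waves 2 to 5), and R2 has three visits. 5 + 3 = 8, which matches the eight time points in the trajectory section, so the original baseline is among them. Mental health is named there. Social support is listed in Table 2 as a potential mechanism of change, and those mechanisms are treated as mediators. Asset accumulation is a Table 2 moderator, and the progress section reports that "Both treatment arms reported a higher increase in their levels of asset possession from baseline to 12 months". Positive youth transitions differ: entry required being in the last two years of primary school, aged 10 to 16 and living in a family, so Wave 1 has little useful variation. Biomarkers were measured only in R2.

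**Who remains?** 1249 × 0.8 = 999; 999 × 0.8 = 799; 799/1383 = 57.8%.

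**Reproducing the protocol's detectable effect for Aim 2.** Inputs from the power section and the study overview: 16 schools per arm, m = 799/48 = 16.65 per school, school ICC .12, within-participant ICC .70, alpha .017 (two-sided assumed), power .80. M = 3 visits.

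- Multiplier: 2.387 + 0.842 = 3.228
- Variance of a school's time-averaged mean, in SD² units: V0 = .12 + [(.70 − .12) + (1 − .70)/3]/16.65 = .12 + .68/16.65 = .1608
- d = 3.228 × √(2 × .1608/16) = .458

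The protocol states .462, so agreement is within 1%. A version using a t distribution with 30 degrees of freedom gives .481.

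**Adding the Wave 1 value.** Let ρ be its correlation with an R2 measurement, taken as equal at all three visits. The article gives no figure across this interval, so ρ is assumed.

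- Person-level reduction only: V = .12 + [.68 − ρ²(1 − .12)]/16.65
- Person and school level: V = .12(1 − ρ²) + [.68 − ρ²(1 − .12)]/16.65

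| ρ (assumed) | Detectable d, person only | Detectable d, person and school | Fall from .458 | Power at d = .458 |
|---|---|---|---|---|
| 0.1 | .457 | .455 | under 1% | about 80% |
| 0.3 | .451 | .435 | 1.5 to 5% | 81 to 84% |
| 0.5 | .439 | .392 | 4 to 14% | 84 to 92% |

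Worked case, ρ = 0.3, both levels: V = .12 × .91 + (.68 − .0792)/16.65 = .1092 + .0361 = .1453; d = 3.228 × √(2 × .1453/16) = .435.

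**The case against.** The strongest reply is that this is an efficiency suggestion and not an error. Several stronger readings are tempting, and the article does not support them.

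- *The H2 comparisons are biased.* Schools were randomised, and an unadjusted randomised comparison is not biased for want of a covariate. Chance school-level imbalance is already reflected in the standard error through the school random intercept. For the same reason, removal of chance imbalance is not a further gain to add to the table: it is the precision gain.
- *T1-RC is misused as a baseline.* It falls years after the intervention, but H2a-H2c average over the R2 visits, so it serves as an outcome visit. The article qualifies the label as following re-consent. The wording biases nothing.
- *Wave 1 is thrown away.* The trajectory analyses use it, although they are exploratory and do not test H2a-H2c.
- *There is no baseline adjustment at all.* Orphanhood status is adjusted for in Aim 1. Whether that carries into the models described as the same approach is not stated. The balance check behind it concerned Original Bridges data, so it does not settle balance in the re-consented subset.
- *Every Aim 2 outcome has a baseline value.* Youth transitions do not have a useful one. Economic stability in R2 rests on bank statements, a savings-account data system and self-report, and no equivalent Wave 1 measure is shown beyond asset possession.

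Selective re-consent is also partly met by the planned maximum likelihood and multiple imputation with auxiliary variables and pattern-based sensitivity analyses. The auxiliary variables are not named, which an article may leave to the analysis plan. They would not by themselves put the Wave 1 value into the analysis model.

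What stands against all this is that the rule forbids a useful covariate for a reason that does not apply to it.

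**Conclusion.** The point holds as a modest, specific improvement. The R2-only rule bars the Wave 1 value of the outcome from the primary Aim 2 and exploratory mental-health models, and its no-reuse reason covers only Waves 2 to 5. The cost is precision, plus some protection against chance and re-consent imbalance when about 58% of those randomised are expected at the final wave. The size depends wholly on an assumed correlation over a long interval: negligible at 0.1, a 1.5 to 5% fall in detectable d at 0.3, and 4 to 14% at 0.5. The upper end of each range needs the covariate to explain school-level as well as person-level variance. The re-consent component cannot be quantified from the article. The primary HIV analysis is not affected.

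**What to change.** Amend the time-points section so that only post-intervention Original Bridges outcomes (Waves 2 to 5) are excluded from the primary and secondary inferential analyses. Prespecify the Wave 1 value as a fixed covariate in the H2 and mental-health models where a comparable measure exists: mental health, social support and assets. Do not attempt this for youth transitions or for biomarkers measured only in R2. State whether the orphanhood adjustment applies to these models too. Tabulate Wave 1 values by arm for the re-consented sample.

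The cost is small: an amended sentence, a merge of data already held, a rule for missing Wave 1 values, and a few degrees of freedom among 48 schools if school means are added. Calling T1-RC the first R2 assessment would be clearer but is optional.

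### Single-step Bonferroni at .05/3 for the three pairwise arm comparisons is valid but less powerful than necessary; a two-sided Shaffer step-down test recovers power within 5% familywise error

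*Protocol article*

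**What the plan says.** Under Primary analyses for Aim 1, H1a (Bridges against control), H1b (Bridges PLUS against control) and H1c (Bridges PLUS against Bridges) are all the pairs that three arms allow: "To test H1a-H1c we will perform three pairwise planned comparisons". Each is held to a fixed threshold: "Alpha (α) will be set at .05/3 = .017 for these three comparisons to maintain a nominal α = .05". No ordering or step-down is described for these tests.

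Primary analyses for Aim 2 repeats the rule for H2a–H2c: "α will be set at .05/3 = .017 to maintain nominal α = .05 per outcome". Secondary exploratory analyses for Aim 1 uses it for its pairwise contrasts too, and there reserves "simulation-based stepdown multiple comparison methods" for additional post-hoc comparisons. The sizing rests on the same level: "We further assume alpha = .017 and power = .80" (Statistical power analysis).

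The article does not say whether tests are one- or two-sided. Each Aim 1 hypothesis is worded directionally: the better-supported arm "will have a lower odds of HIV infection at the final measurement point".

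**The concern.** Bonferroni treats the three nulls as if any combination of them could be true. For pairwise equalities of three arms that is not so. If Bridges differs from control, Bridges PLUS cannot equal both of them. Exactly two true nulls is therefore impossible, and the fixed .05/3 leaves error allowance unused once one null has been rejected.

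The loss falls on the second and third conclusions: showing that both match rates work, or separating one match rate from the other. The sample is a closed cohort, so power cannot be bought by recruiting more people. By the article's own figures, 80% power needs HIV prevalence to fall from 19.7% to 4.4%, and any smaller effect has less. The testing rule is one of the few things still open to change.

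**Working it through.** **1. The article's own figure.** Inputs from Statistical power analysis: "we assumed a control group HIV prevalence of 19.7" percent, "an intraclass correlation (ICC) of .12 based on our current" Bridges data, final N = 799, alpha .017, power .80. From the overview of the Original Bridges study: 48 schools, 16 per arm.

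- Mean cluster size: 799/48 = 16.65.
- Design effect: 1 + (16.65 − 1) × 0.12 = 2.877.
- Effective n per arm: (799/3)/2.877 = 92.6.
- Two-proportion test with pooled variance under the null, two-sided .017, power .80: detectable difference 15.33 points (15.35 at exactly .05/3). The article gives 15.3, so it reproduces.
- One-sided at .017 gives 14.3 points. The sizing therefore points to two-sided tests, although the text does not say so.

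**2. Why the step-down rule controls error (two-sided).** Any two of the three equalities imply the third, so only three cases have a true null:

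- All three true: a false rejection needs the smallest p ≤ .05/3. Probability ≤ 3 × .05/3 = .05.
- Exactly one true: a false rejection needs that contrast's p ≤ .05. Probability ≤ .05.
- Exactly two true: impossible.

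The rule rejects everything Bonferroni rejects, because any p ≤ .05/3 also passes here.

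**3. Power.** Three independent normal arm estimates with equal variance. The design shift for 80% power at two-sided .05/3 is 2.394 + 0.842 = 3.236 standard errors of a contrast. Simulated with 1,000,000 draws:

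| True pattern | Quantity | Bonferroni | Shaffer |
|---|---|---|---|
| Both arms at design effect | each arm vs control | .80 | .86 |
| | both vs control | .69 | .81 |
| | at least one rejection | .913 | .913 |
| Both arms at half effect | each arm vs control | .22 | .26 |
| | both vs control | .10 | .18 |
| | at least one rejection | .34 | .34 |
| Both arms at one third | each arm vs control | .09 | .11 |
| PLUS full, Bridges half | H1a, and likewise H1c | .22 | .35 |

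A separate run of 600,000 draws gave 81.6% for both vs control at the design effect, hence .81–.82. Holm's rule, which ignores the logical link, gives .83 per test and about .74 for both.

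**4. Error in the same model.**

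| True nulls | Bonferroni | Shaffer |
|---|---|---|
| All three | .044 | .044 |
| One (e.g. H1c when both arms work equally) | .017 | .050 |

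**5. With schools as clusters.** Beta-binomial data with 16 schools per arm, 17 participants per school (assumed), ICC .12, and t-tests on school means. At 19.7/4.4/4.4%, power per arm vs control goes from .80 to .88, and for both from .69 to .83; at least one rejection is .923 under either rule. Shaffer's familywise error was .044 with all arms equal, .047 with Bridges equal to control, and .040 with the two intervention arms equal at 4.4%.

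A crude design-effect z-test on the same inputs gave .058 for Shaffer with the two intervention arms at 4.4%. That is small-sample error of the z-test, not of the step-down rule.

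In that z-test simulation, with both arms equally effective, the difference detectable with 80% power per test moves from 15.0 to 14.2 points.

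**The case against.** The strongest reply is that nothing here is wrong. The rule is prespecified, valid and matched to the sizing, and a simple rule for planned contrasts can sit beside a step-down rule for a larger post-hoc family. That stands. A reader might infer that the plan contradicts itself by using the stronger method only for post-hoc tests. It does not; the post-hoc use shows only that the principle is already accepted.

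A reader might also infer that the gain is free. It is not. When both arms work equally, the chance of falsely separating Bridges PLUS from Bridges rises from .017 to .05, and that contrast carries the match-rate question. Familywise error stays within .05, but the extra power comes from spending allowance that Bonferroni leaves unused. A contrast rejected at the second step may also have a Bonferroni-level interval that includes no effect.

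The logic also needs two-sided tests. With directional nulls, Bridges could beat control while PLUS is no better than control and worse than Bridges; both remaining nulls would then be true, and testing each at .05 would not be protected. The sizing supports a two-sided reading, but the text does not state it.

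Finally, the benefit is modest if true effects are well below the design effect, as the half-effect and one-third rows show. That also stands.

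**Conclusion.** The point holds as an efficiency improvement. For two-sided tests of the three pairwise equalities, single-step .05/3 is valid but uniformly no better than the Shaffer rule at the same 5% familywise limit. At the design effect in both arms, the gain is about 6 points of power per comparison with control and about 12 to 13 points for showing both. At half that effect it is about 4 points per test.

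A reader might infer that this remedies a shortage of power. The figures do not support that: the chance of at least one significant result is unchanged, and the detectable difference falls by less than one point.

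The conclusion rests on two-sided testing, on p-values that hold their level with 16 schools per arm, and, for the sizes quoted, on the effect patterns shown and on equal arm variances in the normal model.

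**What to change.** - In Primary analyses for Aim 1, state that tests are two-sided. Test the smallest of the three p-values at .05/3; if it is significant, test the other two at .05 each; otherwise stop.
- Apply the same rule to H2a–H2c per outcome and to the exploratory pairwise contrasts.
- Say that the p-values come from a method that holds its level with 16 schools per arm.
- Note that simultaneous intervals stay at the Bonferroni level and may not match every step-down rejection.
- Keep .017 in Statistical power analysis as a conservative basis.
- Document the change before any comparison by arm is seen. The section on monitoring adverse events has the research team examine preliminary outcome data every quarter, so the timing matters.

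The step-down rule itself needs no new data or model, only the three p-values already planned. Its statistical cost is the higher error for a single true null contrast, still within .05, and the looser match between tests and intervals.
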